### Comparator

The comparison group receives 4 days per week sham-rTMS (using a sham coil) followed by 90 minutes of ERP similar to the other treatment arm. Sham-rTMS delivers pulses at an intensity that is insufficient to affect brain activity but still mimics the sensation on the scalp. As a result, it is considered a null treatment, with any clinical effects in this group attributed to ERP alone. Sham treatment is performed over the same location, that is, pre-SMA, to further ensure blinding of the participant to the treatment condition. Additionally, the other rTMS parameters, 1500 continuous 1-Hz pulses at 110% of the RMT, are identical to those used in the active (verum) condition.

### Co-Intervention: Exposure in Vivo With Response Prevention (ERP)

Prior to the first rTMS-ERP treatment session, 2 ERP preparation sessions without TMS are planned. These sessions are used to motivate participants, reestablish the working mechanisms of ERP, and achieve commitment for active participation in exposure sessions and homework. In addition, participants are helped to define their treatment goals and to link these goals to specific exposure exercises, which can be practiced in either supervised exposure sessions following TMS or at home in unsupervised exposure exercises. ERP is provided according to standard treatment protocols for OCD. Sessions last 90 minutes, which is slightly longer than usual, permitting ERP exercises to take place beyond the confines of the therapist’s office. For this study, a treatment manual has been developed (largely based on the protocol used during the previous TIPICCO trial [19]), consisting of practical information, the time schedule, the agenda to be used in all sessions, and all forms that participants fill in during the treatment (including, for example, those for goals and exercises). Each ERP session follows a similar structure, including a reflection on the prior treatment session, discussing homework exercises, and registering whether homework has been conducted according to plan. Early in the session, clinician-supervised exposure commences in the clinic or outside, depending on the exercise. Clinicians motivate the participant, safeguard against subtle forms of avoidance behavior, and question the participant about the dysfunctional cognition (ie, the prediction the participant expects to occur). When possible, a more realistic alternative cognition is formulated. At the end of the exposure session, homework exercises are planned. ERP is provided by trained and well-supervised clinicians with varying experience and background (registered health care and clinical psychologists, psychologists at entry-level, resident psychiatrists, and behavioral therapy assistants). The clinicians have supervision and intervision every 2 weeks to share experience, discuss exposure exercises, and stagnation in the therapy. Multiple clinicians take responsibility for the treatment of one patient. Doing so enables a 4/wk treatment schedule, decreases the impact of clinician-variables on outcome, and, according to our experience in the TIPICCO-trial, facilitates a strict focus on the exposure during treatment sessions. At the end of the combined rTMS-ERP treatment (after 20, 24, or 28 sessions; see for details adaptive design above), 2 relapse-prevention sessions are scheduled. In these sessions, the possibility of relapse is discussed, and a personalized relapse prevention plan is made. Such a plan is advised in treatment guidelines, helping the participant to recognize early signs of relapse and to take action if necessary. Subsequently, we perform weekly telephone calls for 4 weeks to stimulate continued self-exposure in daily life. After these 4 weeks of self-exposure, we finish with an evaluation session. During the subsequent 1-year naturalistic follow-up phase, participants are allowed to participate in new treatments (but not rTMS) if necessary.

### Blood-Based Biomarkers of Neuroplasticity, Genetics and Multiomics Integration

Blood samples are collected at baseline, posttreatment, and 3-month follow-up in Amsterdam, Nijmegen, and Maastricht. Participants from other centers (Groningen and Eindhoven) are referred to the nearest facility for sampling. After centrifugation, the material is stored at −80 °C following standard operating procedures to ensure uniform handling across sites. Blood-based biomarkers will support identification of neurobiological mechanisms of treatment response and potential predictive markers. The analysis will include:

Genome-wide association study (GWAS): baseline DNA will be isolated from whole blood using standard extraction kits. Genotyping will be conducted with a high-density SNP array, followed by quality control and imputation to a reference panel. Genetic association models will examine baseline variants as predictors of proteomic profiles and clinical outcomes. Polygenic risk scores for OCD and related phenotypes will also be derived.Olink proteomics: plasma samples will be analyzed with Olink panels. Samples from each participant (baseline, posttreatment, and follow-up) will be placed on the same plate to minimize batch variation. A pooled plasma control will be included on each plate to support normalization across assays.SIMOA BDNF isoform quantification: concentrations of mature and pro-BDNF will be measured separately using validated Quanterix SIMOA plasma assays. These analyses will provide isoform-specific validation of Olink findings and clarify treatment-related changes.Exploratory neuron-derived extracellular vesicle (NDEV) analysis: in a subset of 50 participants (150 samples; half receiving real-rTMS and half sham), neuron-derived extracellular vesicles will be isolated via immunocapture. Vesicle lysates will be digested and analyzed using parallel reaction monitoring mass spectrometry targeting BDNF, TrkB, and downstream signaling proteins (eg, ERK, AKT, and CREB). Stable isotope-labeled peptides will enable absolute quantification and evaluate whether peripheral proteomic changes mirror brain-derived molecular signatures.

### Outcome Measures

Primary outcome and primary endpoint:

The primary outcome is the severity of OCD as measured by the Yale-Brown Obsessive-Compulsive Scale I (Y-BOCS-I) [34]. The primary endpoint is the difference between the active and sham intervention groups in posttreatment severity of OCD, estimated using an analysis of covariance (ANCOVA) model that adjusts for pretreatment severity of OCD. The intervention effect will also be reported as a standardized mean difference.

Secondary outcomes - clinical:

Response (=35% reduction on Y-BOCS I) [44].Remission (Y-BOCS I<12) [44].The severity of OCD, as measured using the newer version of the Yale-Brown Obsessive-Compulsive Scale - Y-BOCS II [37,45]. A combined version of the Y-BOCS I and II is administered pretreatment and posttreatment. Additionally, Y-BOCS-II severity scores are collected weekly during treatment and at all follow-up sessions, enabling comparison between the 2 versions and potentially supporting further implementation of the newer Y-BOCS II.The clinical global impression (CGI) severity scale [46].Comorbid depression symptoms, measured using the Beck Depression Inventory (BDI) at baseline, posttreatment, and follow-up [47]. In addition, we administer a VAS for depression at these same time points, plus every week during treatment, to monitor treatment response on mood. The simultaneous administration of VAS and BDI at baseline and posttreatment will allow us to scale and validate the VAS relative to the BDI, while offering a much quicker and simpler assessment for the participants.Anxiety, measured using the Beck Anxiety Inventory (BAI) and a VAS, following the same procedure and rationale as for depression [48].For participants with comorbid tics, as identified using the Yale Global Tic Severity Scale (YGTSS) [49], tic severity will be assessed using the same scale.Tolerability of the treatment and side effects, using an in-house questionnaire developed as part of our previous TIPICCO trial [19].

Secondary outcomes - cost-effectiveness

Societal costs will be measured using the iMTA Productivity Cost Questionnaire (iPCQ) [50] and the iMTA Medical Consumption Questionnaire (iMCQ) [51].QoL (EQ-5D-5L) [52]. Quality-adjusted life-years (QALYs) are the most important outcome measure for health care decision makers when deciding about the reimbursement of health care interventions.

Secondary outcomes - neuroplasticity:

Blood sampling at baseline, directly posttreatment, and at 3-month follow-up is performed to establish markers of treatment-induced neuroplasticity and predictors of treatment response.Pre- and posttreatment MRI scans to analyze ERP and rTMS-induced effects on multiple levels in the brain, using innovative multimodal neuroimaging.Pretreatment structural and functional MRI scans to assess brain structure and network activation and connectivity to predict treatment response.

Exploratory variables:

Patient adherence to treatment protocol, as measured using the Patient Exposure and Response Prevention Adherence Scale (PEAS; [53]) and its relationship to treatment outcome. This scale is carried out by the therapists as part of usual treatment.Difference between responders and nonresponders on circadian rhythm and other sleep disorders at baseline as defined by the Holland Sleep Disorders Questionnaire (HSDQ), as a possible prognostic marker for response [54,55].The relationship of demographic and clinical variables (gender, age, age of onset, medication status), preexisting comorbidities (ie, comorbid tics, depression, anxiety, and autism), and treatment history to the treatment outcome. A simplified Dutch version of the Mini-International Neuropsychiatric Interview (MINI) for *DSM-5*-diagnoses is used to confirm OCD diagnosis and establish current comorbidity [56]. To specifically evaluate symptoms of comorbid autism spectrum disorder, the Dutch version of the Autism Spectrum Questionnaire (AQ-NL) [57] is administered.The Y-BOCS-II symptom checklist [37] is used to categorize symptom dimensions and examine treatment effects and underlying mechanisms in different OCD subgroups.Measuring the exact stimulation location as ascertained and recorded by neuronavigation on 3 separate sessions (session 1, 10, and 20) will allow us to map the variation in achieved location in relation to treatment outcome.Variation in treatment expectancy (7-item credibility and expectancy questionnaire) [58] and blinding success (1-item question “in which condition do you think you were?”) in relation to treatment outcome.

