### Sample Size Calculations

Meta-analyses [41,42] suggest an average effect size of 0.71‐0.79 (Hedges’ g) for the effect of rTMS as monotherapy. Our own meta-analysis [8] showed a lower Hedges’ g of 0.50. We use rTMS in addition to intensive 4-week daily ERP, and we therefore conservatively lowered the expected effect size to 0.4, in line with, for example, the augmentative effect of antipsychotics to either SSRI or cognitive behavioral therapy [59]. The effect size 0.4 corresponds to a pre-post intervention decrease in Y-BOCS I score of 4 points, which we consider a minimal clinically important difference (MCID). Our design uses a 2:1 randomization across the 2 conditions, with twice as many participants in the verum rTMS group. Using a significance level of alpha=.05, a 2-tailed comparison between means, and an estimated power of 0.8, the study requires 150 participants in the verum-rTMS arm and 75 in the sham-rTMS arm. Assuming a 10% dropout rate, we will include (225/0.9=) 250 participants. Participants are considered dropouts if they complete less than 60% of the minimum required 20 rTMS+ERP sessions, corresponding to fewer than 12 sessions. We apply stratified block randomization, with study center as the stratification factor, to ensure balanced allocation of conditions across centers. Although we will take the stratified design into account when analyzing the data by using it as a covariate, we will ignore its effect on the required sample size [60].

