#### Primary Study Parameter

The primary study parameter is the posttreatment effect of the intervention (verum-rTMS vs sham-rTMS) on the primary outcome measure (Y-BOCS I). This effect will be estimated using an ANCOVA model adjusting for baseline Y-BOCS I scores.

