#### Secondary Study Parameters- Clinical

Of the clinical secondary outcomes, response (≥35% reduction in Y-BOCS I) and remission (Y-BOCS I ≤12) will be investigated using generalized linear mixed models (LMM, mixed-effects logistic regression). Pre-to-post changes in Y-BOCS II, CGI score, QoL, depression, tics, and anxiety will be tested using LMM analysis for repeated measures. The model will include fixed effects for time, study center, and the group-by-time interaction, but not for the group indicator alone, in order to adjust for potential baseline differences in the outcome variable. The group-by-time interaction term represents the between-group intervention effect and therefore constitutes the primary parameter of interest. Tolerability and side effects will be reported as absolute numbers and described qualitatively.

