#### Exploratory Moderators and Mediators of Treatment Response

The exploratory outcomes and parameters that will be investigated as modifiers of treatment response include expectation of outcome, participant treatment adherence, circadian rhythm, sleep disorders, and medication status. Depending on the results, additional moderator and mediator analyses will be carried out.

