## Discussion

### Anticipated Findings

This study protocol outlines the first adequately powered multicenter RCT investigating the efficacy and cost-effectiveness of the pre-SMA-rTMS protocol compared to sham-rTMS as adjuvant therapy to ERP in adults with OCD who did not adequately respond to prior first-line treatment. The RCT aims to assess both the clinical efficacy and cost-effectiveness of rTMS targeting the pre-SMA in this population. Alongside the primary focus on efficacy and cost-effectiveness, the study also incorporates several exploratory biological outcome measures designed to shed light on the mechanisms underlying variation in treatment response and short- and long-term treatment-induced neuroplasticity. These measures may ultimately contribute to identifying and developing biomarkers that can inform treatment decisions beyond standard clinical assessments.

It is hypothesized that rTMS combined with ERP will be more efficacious and cost-effective compared to sham-rTMS and ERP. Additionally, we also expect clinical effects (Y-BOCS reduction) in the sham-rTMS group, as both groups receive an intensive format of ERP at expert centers for OCD. The clinical outcomes in the verum group may be comparable to those observed in our previous TIPICCO trial (Clinical Trial ID: NCT03667807 [19], which demonstrated a significant reduction in symptoms (Cohen *d*=1.66, Δ Y-BOCS = −10.836, *P*<.001, 95% CI −12.504 to −9.168) and a 57.4% response rate across 3 different rTMS protocols combined with ERP in a comparable participant group. Participants in that trial received fewer treatment sessions (16 vs 20‐28), shorter ERP sessions (60 vs 90 min), and different TMS protocols (eg, 10 Hz pre-SMA); however, this may allow for improved outcomes in this study.

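### Testing baseline sleep as a prognostic marker by comparing responders with nonresponders gives up over a third of the information in the continuous Y-BOCS I

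*Protocol article*

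**What the plan says.** In the protocol article, Outcome Measures lists under its exploratory variables: "Difference between responders and nonresponders on circadian rhythm and other sleep disorders at baseline as defined by the Holland Sleep Disorders Questionnaire (HSDQ"). The purpose given is "as a possible prognostic marker for response". The items beside it on adherence, demographic and clinical variables, stimulation location, and expectancy and blinding are each related to outcome in general, with no dichotomy named.

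Secondary Study Parameters - Clinical defines the dichotomy: "response (≥35% reduction in Y-BOCS I"). Primary Study Parameter uses the same scale as a continuous score: "This effect will be estimated using an ANCOVA model adjusting for baseline Y-BOCS I scores".

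Exploratory Moderators and Mediators of Treatment Response gives sleep a second role. The variables to be "investigated as modifiers of treatment response" "include expectation of outcome, participant treatment adherence, circadian rhythm, sleep disorders, and medication status". No model is given there.

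**The concern.** The sleep item names a specific contrast, so this is a stated choice and not a detail left open. Splitting participants at a 35% reduction treats someone who improved by 34% as different from someone at 36%, and as the same as someone who did not improve at all. The information within each group is discarded although the Y-BOCS I has been collected and is modelled continuously elsewhere in the plan. A real but modest association between poor sleep and outcome is then more likely to be missed, and a null result is harder to interpret.

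**Working it through.** **Inputs from the protocol article**
- Sample Size Calculations: standardized effect 0.4, 2:1 allocation, 150 verum and 75 sham (225 evaluable), 10% dropout, 250 enrolled. The design is set "Using a significance level of alpha=.05, a 2-tailed comparison between means, and an estimated power of 0.8".
- Anticipated Findings: "a 57.4% response rate across 3 different rTMS protocols combined with ERP in a comparable participant group". This is the only response rate in the article.

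**Assumptions not in the article**
- The outcome underlying the response cut is roughly normal.
- The sleep–outcome association is weak.
- The response rate is varied from 20% to 80%, because the 57.4% comes from a trial of three rTMS protocols and one third of participants here receive sham.

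**Step 1. The plan's own figure.** Sham arm: (1 + 1/2) × (1.960 + 0.842)² / 0.4² = 73.6, rounded up to 74. That gives 148 verum and 222 in total. A t-test calculation gives 74.2 for the sham arm, hence 75 and 150. Power at 75/150 is 0.804 by t-test and 0.807 by the normal approximation. Then 225 / 0.9 = 250. The stated sample size reproduces. The article gives no power figure for the sleep analysis.

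**Step 2. Information kept by the split.** For a weak association, the efficiency of a dichotomised outcome relative to the same outcome kept continuous is φ(z_p)² / [p(1 − p)], where p is the response rate and φ is the normal density at its quantile.

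At p = 0.574: z_p = 0.187 and φ = 0.392, so 0.392² / (0.574 × 0.426) = 0.1537 / 0.2445 = 0.629. The loss is 37.1%, and 225 × 0.629 ≈ 141.

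| Response rate | Efficiency | Loss | 225 act like |
|---|---|---|---|
| 50% | 0.637 | 36.3% | 143 |
| 45% or 55% | 0.633 | 36.7% | 142 |
| 57.4% | 0.629 | 37.1% | 141 |
| 40% or 60% | 0.622 | 37.8% | 140 |
| 30% or 70% | 0.576 | 42.4% | 130 |
| 20% or 80% | 0.490 | 51.0% | 110 |

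The smallest possible loss, at 50%, is 1 − 2/π = 36.3%.

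**Step 3. What this means for power (illustration).** With Fisher's z and n = 225, the correlation detectable with 80% power on the continuous score is tanh[(1.960 + 0.842) / √222] = 0.186. The split attenuates it to 0.186 × √0.629 = 0.147. Power is then Φ[atanh(0.147) × √222 − 1.960] ≈ 0.60. To regain 80% power the true correlation would have to be 0.186 / √0.629 = 0.234.

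**Step 4. Simulation check.** 3,000 simulated trials of 150 + 75 participants were run, with a purely prognostic sleep slope of 0.19 SD and the cut placed at 57.4% responders. Power was 61% for the responder comparison and 81% for the continuous outcome adjusted for arm, in line with step 3.

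**Step 5. The modifier question.** In the same set-up, sleep slopes of opposite sign in the two arms were simulated so that they cancel overall. A responder comparison that ignores arm rejected in 5% of runs, the alpha level. An HSDQ-by-arm term had 81% power. The modifier question therefore needs its own model, whichever prognostic analysis is chosen.

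**The case against.** A responder comparison answers a legitimate question. Response is a declared secondary outcome, and a marker for response is not the same thing as a predictor of severity. Response is also a cut of percentage change, whereas a regression would use the posttreatment score adjusted for baseline, so the efficiency formula only approximates the loss between those two analyses. The HSDQ may be used as categories instead of a score. Nothing confirmatory depends on the result.

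Most of this stands as a limit on precision and importance. It does not remove the point. The loss arises from cutting the outcome and has a floor of 36% whatever the response rate. The neighbouring exploratory items are not tied to a dichotomy, and no reason is given for treating sleep differently. Categorical use of the HSDQ would change the correlation illustration, but the loss from cutting the outcome would remain. The responder comparison can be kept beside the regression.

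A reader might go further and infer that the plan pools the arms and so fails to test the modifier role it assigns to sleep. The article does not support that. The sleep item does not say that arms are pooled, and it states a prognostic aim only. The modifier question is assigned separately, without a model, and the Dissemination Plan says all analysis plans will be preregistered. The absence of an interaction model from the article is not a finding.

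**Conclusion.** The point holds for the prognostic analysis. Comparing responders with nonresponders loses about 36–38% of the information at response rates of 40–60%, 37% at the borrowed 57.4%, and more outside that range. At 57.4%, 225 evaluable participants carry the information of about 141. These figures assume a roughly normal outcome and a weak association. The drop in power from 80% to about 60% is an illustration at a correlation of 0.186, which the article does not state.

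On modification, the conclusion is limited. A responder comparison without arm could not answer that question, but the article does not claim that it does. The importance is low, because the analysis is exploratory and the primary result and the sample size are unaffected.

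**What to change.** - **Prognostic analysis:** regress posttreatment Y-BOCS I on baseline HSDQ, baseline Y-BOCS I, arm and centre. Report the HSDQ coefficient with its confidence interval.
- **Modifier analysis:** fit a second model that adds HSDQ-by-arm and read only the interaction from it. Take the prognostic effect from the model without that term. Once the interaction is included with arm coded 0/1, the HSDQ coefficient is the slope in the reference arm and no longer the overall prognostic effect.
- **Responder comparison:** keep it as a descriptive table.

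The cost is two regression models in place of a two-group comparison, with no new data. The article reports enrolment as still under way, so the change can go into the preregistered analysis plan before unblinding.

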### Blinding

Participants, ERP therapists, and those carrying out clinical and cognitive assessments are blinded to treatment conditions. The rTMS treatment administrators are not blinded due to the technical nature of this treatment; however, they are instructed not to disclose treatment allocation to participants, therapists, or blinded assessors.

### Sample Size Calculations

Meta-analyses [41,42] suggest an average effect size of 0.71‐0.79 (Hedges’ g) for the effect of rTMS as monotherapy. Our own meta-analysis [8] showed a lower Hedges’ g of 0.50. We use rTMS in addition to intensive 4-week daily ERP, and we therefore conservatively lowered the expected effect size to 0.4, in line with, for example, the augmentative effect of antipsychotics to either SSRI or cognitive behavioral therapy [59]. The effect size 0.4 corresponds to a pre-post intervention decrease in Y-BOCS I score of 4 points, which we consider a minimal clinically important difference (MCID). Our design uses a 2:1 randomization across the 2 conditions, with twice as many participants in the verum rTMS group. Using a significance level of alpha=.05, a 2-tailed comparison between means, and an estimated power of 0.8, the study requires 150 participants in the verum-rTMS arm and 75 in the sham-rTMS arm. Assuming a 10% dropout rate, we will include (225/0.9=) 250 participants. Participants are considered dropouts if they complete less than 60% of the minimum required 20 rTMS+ERP sessions, corresponding to fewer than 12 sessions. We apply stratified block randomization, with study center as the stratification factor, to ensure balanced allocation of conditions across centers. Although we will take the stratified design into account when analyzing the data by using it as a covariate, we will ignore its effect on the required sample size [60].

